# LIST OF ABBREVIATIONS

| **AKI** | Acute Kidney Injury |
| --- | --- |
| **AL** | Anastomotic Leak |
| **AUR** | Acute Urinary Retention |
| **BMI** | Body Mass Index |
| **CDC** | Centers for Disease Control and Prevention |
| **CVA** | Cerebrovascular Accident |
| **DGE** | Delated Gastric Emptying |
| **DSMB** | Data Safety Monitoring |
| **dSSI** | Deep Surgical Site Infection |
| **eGFR** | Estimated Glomerular Filtration Rate |
| **Kcal** | Kilocalorie |
| **Kg** | Kilogram |
| **LOS** | Length of stay |
| **MCID** | Minimally Clinical Important Difference |
| **MI** | Myocardial Infarction |
| **MINS** | Myocardial Injury After Non-Cardiac Surgery |
| **PJI** | Prosthetic Joint Infection |
| **POI** | Prolonged Postoperative Ileus |
| **PONV** | Postoperative Nausea and Vomiting |
| **QoL** | Quality of Life |
| **RCT** | Randomized Controlled Trial |
| **SF-36** | 36-Item Short Form Survey |
| **SSI** | Surgical Site Infection |
| **sSSI** | Superficial Surgical Site Infection |
| **UTI** | Urinary Tract Infection |
| **VLED** | Very Low Energy Diet |
| **VTE** | Venous Thromboembolism |

# STUDY SYNOPSIS

| **Title** | PReoperative very low Energy diets for obese PAtients undergoing non-bariatric surgery Randomized Evaluation (PREPARE) Pilot Trial |
| --- | --- |
| **Principal Investigators** | [name], [name], and [name] |
| **Sponsor** | None |
| **Project Office** | St. Joseph’s Healthcare Hamilton, [name] |
| **Study Design** | Multi-center blinded, parallel pilot randomized controlled trial at Hamilton Health Sciences, St. Joseph’s Healthcare Hamilton, and Kingston Health Sciences. |
| **Study Population** | **Inclusion criteria**   - Older than 18 years of age - BMI of greater than 30 kg/m^2^ - Undergoing elective non-bariatric surgery for benign or malignant disease   **Exclusion criteria**   - Undergoing bariatric surgery (i.e., gastric bypass, gastric sleeve, duodenal switch) - Undergoing ophthalmologic or neurologic surgery - Undergoing wide local excisions for skin and/or subcutaneous lesions - Undergoing endoscopic surgery - Undergoing urgent or emergent surgery - Recently diagnosed myocardial infarction or unstable angina (i.e., within six months of assessment for trial enrolment) - Diagnosed moderate-to-severe renal dysfunction (i.e., eGFR less than 30mL/min/1.73m^2^) - Diagnosed severe liver dysfunction (i.e., cirrhosis, portal hypertension, hepatic encephalopathy, hepatorenal syndrome) - Recently diagnosed alcohol or drug use disorders (i.e., excessive use of substance within six months of assessment for trial enrolment) - Experienced a recent episode of gout (i.e., within six months of assessment for trial enrolment) - Medical history of porphyria - Known allergy to any Optifast® ingredient - Enrolled in other prospective studies with similar interventions and/or outcomes - Pregnant or breastfeeding women - Patients residing in a long-term care facility - Patients otherwise unable to provide written informed consent |
| **Sample Size** | This multicenter pilot randomized controlled trial will enrol 88 patients. |
| **Study Intervention** | The intervention being investigated is the use of Optifast® 900 or Medimeal® program for three weeks preoperatively plus preoperative standard of care |
| **Study Control** | Preoperative standard of care consisting of surgeon-delivered preoperative weight loss counselling at the time of the preoperative clinic visit |
| **Feasibility Objectives** | The feasibility objectives of this trial are:   1. Determine the feasibility of recruiting patients in a timely manner across local and outside sites. 2. Determine compliance with preoperative VLEDs in obese patients undergoing elective non-bariatric surgery. 3. Determine the feasibility of completion of follow up. 4. Determine our ability to develop a network of participating sites in a multi-site initiative. 5. Determine the safety of administering preoperative VLEDs to obese patients undergoing elective non-bariatric surgery. |
| **Full Trial Objectives** | The overall trial objectives are:   1. Determine the impact of preoperative VLEDs on postoperative morbidity in obese patients undergoing non-bariatric surgery. 2. Determine the ability for preoperative VLEDs to effectively induce significant weight loss in obese patients undergoing non-bariatric surgery. 3. Determine the effect of preoperative VLEDs on intraoperative difficulty as measured by operative time, intraoperative blood loss, and surgeon perceived difficulty. |
| **Feasibility Outcomes** | The primary outcome will be feasibility for an adequately powered randomized controlled trial. Feasibility will be measured according to the following:   1. Recruitment rate: number of patients enrolled and randomized into the trial per month. A rate of 16 patients per month (4 patients per site per month) is considered acceptable. 2. Intervention compliance: Defined as the number of doses taken will be divided by the total number of doses prescribed (84) for each participant randomized to the intervention arm. A mean compliance of greater than 80% (i.e., completing 80% or more of their VLED doses), is the benchmark for feasibility in the present study. 3. Follow-up completion: Defined as completion of patients pre-VLED, preoperative, and 30-day postoperative visits and completion of the anthropometric measures and study questionnaires. A follow-up completion rate of greater than 90% will support the feasibility of a larger RCT. |
| **Full Trial Outcomes** | The outcomes for the overall trial will be:   - Overall 30-day postoperative morbidity - 30-day system-specific complications - 30-day postoperative mortality - Preoperative weight loss - Operative time - Intraoperative blood loss - Postoperative length of stay - Quality of life |
| **Statistical Considerations for the Feasibility Study** | Feasibility Objectives: Descriptive statistics (means, medians, standard deviations, interquartile ranges, proportions) will be used to characterize the study sample. The outcomes of the pilot study are largely descriptive in nature and will focus on feasibility as opposed to statistical comparisons.  Overall Trial Objectives: We will not assess statistical significance for the overall trial clinical outcomes. However, we will calculate aggregated measures for 30-day postoperative morbidity to ensure an accurate power calculation is performed for the fully powered trial. |
| **Duration of Study Period (per patient)** | Patients will complete a course of Optifast® 900 or Medimeal® during the three weeks preceding their operative date. They will be followed throughout their index postoperative stay in hospital. They will then have follow-up at 30-days postoperatively. |

# LAY SUMMARY

Obesity has reached epidemic proportions worldwide affecting 700 million persons worldwide, representing 11% of the world’s population. The economic costs of obesity are devastating with an estimated $2.5 trillion and over $100 billion in the United States and Canada, respectively. The obese surgical patient is increasingly pervasive, which may have significant economic and clinical consequences. Obesity in the surgical setting can be extremely challenging and is associated with increased risk of both intraoperative and postoperative complications. Weight loss prior to surgery can significantly reduce these risks and contribute to enhanced postoperative recovery. Yet, preoperative optimization for obese patients has been sporadically applied and studied outside of bariatric surgery. In bariatric surgery, a surgical sub-specialty that manages obese patients almost exclusively, an intensive preoperative optimization program exists. As part of this, patients adhere to very low energy diets (VLEDs) with liquid formulations for two-to-three weeks prior to surgery in an attempt to reduce overall fat volume and improve operative conditions. Despite routine use in bariatric surgery, VLEDs have only been employed in a small number of studies evaluating obese patients undergoing non-bariatric surgery. Evidence for this low-cost initiative is promising but inconclusive. As such, we have designed a pilot randomized controlled trial (RCT) aimed at assessing the feasibility and safety of performing an adequately powered RCT for assessing efficacy of VLEDs with liquid formulation in obese patients undergoing elective non-bariatric surgery. If this pilot RCT demonstrates feasibility and safety, we will be armed with the knowledge required to pursue a larger, adequately powered, multicenter RCT with the intent of optimizing this patient population prior to elective non-bariatric surgery. Ultimately, we hope this research program can inform a preoperative optimization pathway for these patients with the aim of improving outcomes and decreasing associated healthcare burden.

# THE NEED FOR A TRIAL

## What is the problem to be addressed?

Obesity is a worldwide pandemic affecting upwards of 700 million people around the globe.^1^ The economic burden is estimated at over $2 trillion United States dollars (USD) and the resultant healthcare consequences can be devastating for systems and patients alike.^2^ Obesity adversely affects nearly all human physiologic function. It increases the risk of developing insulin resistance, cardiovascular disease, several types of cancers, mental health concerns, and more.^1,3,4^ Numerous public health campaigns have been developed with the aim of preventing these comorbidities, but these patients remain pervasive, and present significant challenges in managing acute medical and surgical conditions. Unfortunately, as of now, this problem is only set to magnify as up to 20% of children and adolescents in the United States are obese.^5^

Obese patients presenting in need of medical and surgical intervention are at higher risk of prolonged hospitalization, infectious morbidity, and venous thromboembolism.^6–8^ In the postoperative period in particular, their risk of morbidity is significantly heighted.^9^ Obese patients are at double the risk of postoperative cardiovascular, genitourinary, and wound complications as compared to their non-obese counterparts.^9,10^ Prolonged hospitalization and increased healthcare costs result.^11,12^

To pre-emptively mitigate some of these concerns prescribed preoperative weight loss via very low energy diets (VLED) is standard of care for patients undergoing bariatric surgery.^13^ These programs can effectively induce significant amounts of preoperative weight loss in these obese patients.^14–16^ This contributes to decreased postoperative length of stay (LOS), as well as decrease surgeon perceived technical difficulty.^17,18^ The impact on postoperative morbidity, however, is less clear. We performed a systematic review and meta-analysis which suggested a trend towards a significant reduction in postoperative morbidity in bariatric surgery patients, but the pooled analysis remained underpowered to adequately assess this outcome.^14^

VLEDs have only been sporadically applied and studied outside the setting of bariatric surgery.^19^ Safety and efficacy have been demonstrated in small, mostly observational studies evaluating patients undergoing both benign and malignant non-bariatric surgery, yet adequately powered prospective randomized study and the use of preoperative VLEDs in this patient population remains limited.^19^ As such, we propose to conduct a multi-center randomized controlled trial (RCT) aimed at determining the efficacy of contemporary VLEDs in obese patients undergoing a variety of non-bariatric surgeries. Ultimately, we plan on evaluating the efficacy of VLEDs as a preoperative intervention for inducing weight loss and improving perioperative outcomes via an adequately powered RCT. This is a reasonable next step given the trend towards a decrease in postoperative morbidity in bariatric surgery patients despite an underpowered analysis in addition to the sporadic study of this intervention in patients undergoing non-bariatric surgery. Prior to proceeding with a adequately powered RCT, however, a pilot RCT is warranted to confirm feasibility. Given that VLEDs are a complex intervention, assessing patient compliance with the diet and the required follow-up for data collection is crucial prior to embarking on pursuit of a multi-center international RCT.

## What is/are the principal research question(s) to be addressed?

### Feasibility Objectives:

The objective of this pilot RCT is to determine the feasibility of a multicenter, blinded RCT comparing obese patients (i.e., body mass index [BMI] greater than 30kg/m^2^) receiving VLEDs versus control prior to elective non-bariatric surgery in terms of perioperative outcomes.

The specific feasibility objectives of this trial are:

1. Determine the feasibility of recruiting patients in a timely manner across local and outside sites.
2. Determine compliance with preoperative VLEDs in obese patients undergoing elective non-bariatric surgery.
3. Determine the feasibility of completion of follow up.
4. Determine our ability to develop a network of participating sites in a multi-site initiative.
5. Determine the safety of administering preoperative VLEDs to obese patients undergoing elective non-bariatric surgery.

### Full Trial Objectives:

The objective of the fully powered multicenter, blinded RCT will be to compare obese patients receiving a VLED prior to elective non-bariatric surgery to obese patients receiving a control in terms of 30-day overall postoperative morbidity.

The specific efficacy objectives will be:

1. Determine the impact of preoperative VLEDs on postoperative morbidity in obese patients undergoing elective non-bariatric surgery.
2. Determine the ability for preoperative VLEDs to effectively induce weight loss in obese patients undergoing elective non-bariatric surgery.
3. Determine the effect of preoperative VLEDs on intraoperative difficulty as measured by operative time, intraoperative blood loss, and surgeon perceived difficulty.

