## Why is a trial needed now?

Obesity is increasingly prevalent in Western society.^20^ There are over 90 million obese individuals living in the United States alone, with over half of the population projected to be obese by 2030.^21^ The obese surgical patient has become unavoidable across all surgical specialties. In abdominal surgery, these patients can present unique problems due to increased intraoperative difficulty associated with both subcutaneous and visceral fat volume.^22–25^ ^26,27^Intraoperatively, obesity is associated with increased operative time, blood loss, and surgeon perceived technical challenge.^26^ Postoperative care can present similar difficulty, as obesity is associated with increased risk of surgical site infections, urinary tract infection, pulmonary complications, wound dehiscence, venous thromboembolism, and more.^7,27,28^ Obesity may even be associated with worse long-term oncologic outcomes following resection of solid tumors.^29,30^

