## What are the proposed practical arrangements for allocating participants to trial groups?

Patient recruitment will occur at Hamilton Health Sciences, St. Joseph’s Healthcare Hamilton, and Kingston Health Sciences. All surgeons who perform elective non-bariatric surgery at these sites will be made aware of the study via workshops and internal communications. Patients will be identified by the surgeons, their administrative assistants, and/or study investigators at the time of referral, at the time of their initial preoperative consultation, or some time following their initial preoperative consultation. Surgeons and/or other clinicians within a patient’s circle of care will introduce the study to participants at the time of their preoperative visits or sometime thereafter. Patients may also reach out directly to study investigators via the contact information provided on the study poster should they choose. Patients meeting inclusion criteria based on a review of their electronic medical record, which will only be accessed by persons within the circle of care or researchers that have obtained permission from the patient, will have their contact information (i.e., email and phone number) recorded and provided to designated research personnel at the time of their initial surgical consultation in clinic. This email contact information will then be passed into a novel automated clinical trials platform developed by Phelix AI©. This platform will automatically send an electronic version of the written informed consent document to the patient as well as a link to schedule an appointment in the following 1-2 days with the research team to discuss the informed consent document via telephone. If the Phelix AI© platform identifies that the patient does not have an accessible email address, this will trigger a notification to the research team and prompt them to call the patient by telephone. At the time of initial contact between the study personnel and patient, the study will be introduced, eligibility will be confirmed. Patients will be provided with the opportunity to ask questions about the previously circulated ICF, and if they have yet to review the document, they will review the document in its entirety with the research team at the time of the telephone contact. If, at the end of this process, patients are understanding of the material risks and benefits of participation, and wish to be enrolled in the study, they will sign the ICF and subsequently be randomized to one of the two arms in this parallel RCT. Following ascertainment of written informed consent, patients will be randomized via a web-based randomization system (randomization.net) in a 1:1 fashion to receive either standard of care plus preoperative VLED or standard of care alone. Randomization will be according to variable block sizes of four and six and will be stratified according to centre.

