4. Follow-up completion: Defined as completion of the pre-VLED, preoperative, and thirty-day postoperative visits, along with complete anthropometric measures and study questionnaires. A follow-up completion rate of greater than 90% will support the feasibility of a larger RCT. A follow-up completion rate of 80-90% will be considered feasible with modifications for the adequately powered RCT. A follow-up completion rate of less than 80% will suggest that a larger RCT is not feasible.

Safety Outcomes:

The primary safety outcome will be adverse events deemed secondary to the Optifast® 900 or Medimeal® programs. The adverse events will be recorded as dichotomous outcomes and described as either minor or serious, in a similar fashion to the OPTIWIN Study; the largest medical weight loss RCT evaluating Optifast®.^41^ Standardized definitions for minor and major adverse events are described in “Adverse Events” associated document. We will also measure patient frailty with grip strength at the time of anthropometric measurement.^43^

Clinical Outcomes:

The efficacy outcomes will include:

1. Overall 30-day postoperative morbidity. This will be defined as any deviation from the usual postoperative course within 30-days of the index operation and will be a composite of system-specific complications (see “Trial Outcome Definitions” document)
2. 30-day system-specific complications (see “Trial Outcome Definitions” document)
3. 30-day postoperative mortality
4. Preoperative weight loss. Preoperative weight loss will be assessed by measuring the post-VLED weight on the date of surgery and adjusting for the baseline weight in kilograms, as measured in a standardized fashion by a blinded research assistant.
5. Operative time. Operative time was chosen as an outcome as it is a commonly used objective surrogate for operative difficulty across various types of surgery.^44–46^ It has been used in previous bariatric RCTs as the primary outcome.^47^ Operative time will be measured as the time between first skin incision and closure of the last surgical wound in minutes and will be retrieved from the patient electronic medical record.
6. Intraoperative blood loss. This will be measured in milliliters and will be ascertained from the patient chart.

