## What is the planned recruitment rate? How will recruitment be organized?

The anticipated recruitment rate will be 16 patients per month. Patient enrollment will continue until 88 patients are enrolled (i.e., approximately 5.5 months). There are over 200 elective non-bariatric abdominal surgeries performed monthly across the four included sites, and approximately 26.6% of Canadians are obese, which equates to approximately 53 patients per month that may be potentially eligible for enrollment.^50^ Moreover, there are over 400 elective orthopedic surgeries performed monthly across the four included sites, and given the same prevalence of obesity as above, this would equate to another approximate 106 obese patients per month that may be potentially eligible for enrollment.^50^ There are over 200 cardiac surgeries performed per month at our cardiac surgery center, equating to another 53 potentially obese patients eligible per month. Across Otolaryngology, Plastic Surgery, and Neurosurgery, there are at least another 200 elective cases performed per month, thus another 53 potentially eligible obese patients per month. Altogether, there will likely be over 250 potentially eligible patients per month.

All surgeons who perform elective non-bariatric surgery will be asked to consent to allow their patients to be approached. Patients will be identified from outpatient clinic schedules via the institution’s (i.e., Epic) or surgeon’s (e.g., Oscar) electronic medical record. Upon review of their chart, should the patient meet inclusion criteria and not meet any apparent exclusion criteria, they will be approached by research personnel who will provide further details with regards to the RCT. Recruitment will be organized and implemented by [name] and the research assistant(s) under the guidance of the coordinating center and steering committee.

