## What are the proposed types of analyses?

Descriptive statistics (means, medians, standard deviations, interquartile ranges, proportions) will be used to characterize the study sample. The outcomes of the pilot study will be descriptive in nature and will focus on feasibility. Binary outcomes will be described using proportions with corresponding 95% CIs estimated using the Wilson Score method. Differences in continuous outcomes will be described using the difference in means with corresponding 95% CIs. Considering the feasibility nature of this pilot study, and following the 2010 CONSORT statement, we will not assess statistical significance for outcomes.^53^ We will calculate aggregated measures for 30-day postoperative morbidity to compare this to the tentative power calculation in the “Full Trial Power Calculation” associated document, to ensure an accurate power calculation is performed for the fully powered RCT. The proposed data analysis plan for the full RCT is reported in the “Full Trial Statistical Analysis Plan” associated document. Data will be analyzed using STATA statistical software (StataCorp version 15; College Station, TX). All data analysis will be completed by a blinded statistician.

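### In the pilot, operative time and blood loss are pooled over very different operations and compared by raw means: unbiased, but less precise than they need be

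*Protocol*

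**What the plan says.** Objective 3 stands in the protocol under Full Trial Objectives, and again in the synopsis: "Determine the effect of preoperative VLEDs on intraoperative difficulty as measured by operative time, intraoperative blood loss, and surgeon perceived difficulty".

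The outcome section fixes the scales. For operative time: "Operative time will be measured as the time between first skin incision and closure of the last surgical wound in minutes". For blood loss: "This will be measured in milliliters and will be ascertained from the patient chart". Operative time is justified on the ground that "it is a commonly used objective surrogate for operative difficulty across various types of surgery".

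The inclusion criteria admit any major elective operation under general anaesthetic whose incision goes deeper than the subcutaneous layer. The recruitment section counts potentially eligible obese patients per month as about 53 abdominal, 106 orthopaedic, 53 cardiac and 53 from three other specialties. For the largest group it says that "there are over 400 elective orthopedic surgeries performed monthly across the four included sites".

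On allocation: "Randomization will be according to variable block sizes of four and six and will be stratified according to centre". On the pilot analysis: "Differences in continuous outcomes will be described using the difference in means with corresponding 95% CIs". That section names no covariate and rules out significance testing, and no subgroup analyses are planned. It refers the full trial's analysis to a separate document that is not at hand.

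**The concern.** Minutes and millilitres say something about difficulty when like operations are compared. Pooled over joint replacement, bowel surgery and cardiac surgery, much of their spread may come from which operation was done. The planned operation is known before randomisation, because eligibility depends on it, yet neither the allocation nor the stated pilot estimator uses it.

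The protocol's own rationale for difficulty is partly specific to one field: "In abdominal surgery, these patients can present unique problems due to increased intraoperative difficulty associated with both subcutaneous and visceral fat volume". Abdominal surgery is about one fifth of the counted pool.

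At stake is the precision of the pilot's operative-time and blood-loss differences, and how far a chance excess of long operations in one arm can move them. The feasibility outcomes, which are primary, are not affected.

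**Working it through.** **1. Figures the protocol gives.** It gives no mean, SD or interval for operative time or blood loss. Its one precision figure, for 90% follow-up completion in 88 patients, reproduces: the Wilson interval is 82.0% to 94.7%, against the stated 82–95%. It has no bearing on this point. The pool counts also reproduce: 200 × 0.266 = 53.2 and 400 × 0.266 = 106.4. The total is 53 + 106 + 53 + 53 = 265, so the shares are 20/40/20/20%. All operative times below are assumptions.

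**2. Bias.** A simulation used no true effect, 44 per arm, assumed means of 150/90/240/120 minutes (abdominal/orthopaedic/cardiac/other), a within-group SD of 45 and 10,000 runs. The unadjusted difference averaged −0.1 minutes, so operation type does not bias the comparison.

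**3. Chance imbalance, ignoring centre.** For a specialty with a 20% share:

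SD of the arm difference in share = √(2 × 0.2 × 0.8 / 44) = 0.085; 1.96 × 0.085 = 0.167, or about ±17 points.

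The chance of a gap of 10 points or more is about 23%. If that specialty runs 60, 120 or 180 minutes longer than the rest, ±17 points moves the mean difference by about ±10, ±20 or ±30 minutes. The 95% interval already allows for this movement, so it is not a second harm on top of the wider interval.

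**4. Precision, by formula.** With between-group variance B and within-group SD W:

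unadjusted SE = √(B + W²) × √(2/44); adjusted SE = W × √(2/44).

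For means of 150/90/240/120 the overall mean is 138, and B = 0.2 × 12² + 0.4 × 48² + 0.2 × 102² + 0.2 × 18² = 3,096. With W = 45:

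- unadjusted SE = √(3,096 + 2,025) × 0.213 = 15.3, so the half-width is 29.9 minutes
- adjusted SE = 45 × 0.213 = 9.6, so the half-width is 18.8 minutes
- share of variance due to operation type = 3,096 / 5,121 = 60%

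**5. Precision, by simulation.** 88 patients, skewed (lognormal) times, 3,000 replicates, with and without operation-group terms. The last column is 1 − 1/ratio².

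| Assumed means (min) | Within-group CV | SE ratio, unadjusted to adjusted | Variance due to operation type |
|---|---|---|---|
| 120/90/150/90 | 0.3 | 1.20 | 31% |
| 120/90/150/90 | 0.5 | 1.07 | 13% |
| 150/90/210/90 | 0.3 | 13.3 / 8.8 = 1.51 | 56% |
| 150/90/210/90 | 0.5 | 17.8 / 14.6 = 1.22 | 33% |
| 180/90/270/90 | 0.3 | 1.81 | 69% |
| 180/90/270/90 | 0.5 | 1.32 | 43% |

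For the middle means the half-widths are 1.96 × 13.3 = 26 and 1.96 × 17.8 = 35 minutes unadjusted. Adjusted, they are 1.96 × 8.8 = 17 and 1.96 × 14.6 = 29 minutes.

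A more extreme set (180/75/300/150 with a constant SD of 30) gives half-widths of 36.9 and 12.5, a ratio of 2.95. It implies a CV of only 30/300 = 0.1 in the longest group, so I do not rely on it.

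**6. Allowing for centre stratification.** The recruitment section places cardiac surgery at a single centre. A 20% share of 88 is about 18 patients, which would be about 80% of a 22-patient site. Balanced allocation within that site gives an SD for the cardiac imbalance of √(2 × 11 × 0.8 × 0.2) / 44 = 0.043. So ±17 points becomes about ±8.

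Repeating the six scenarios with all cardiac cases at one site gives SE ratios of 1.03 to 1.39. With cardiac cases spread over sites they are 1.08 to 1.80. The smaller ratios describe the true standard error. A plain two-sample interval takes no credit for centre stratification, so its printed width would not shrink accordingly. That is a reason to put centre in the model too.

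**The case against.** The strongest objection is that objective 3 belongs to the full trial. Its analysis plan is a separate document, and the mean difference quoted above describes the pilot. This stands. A reader might infer that the full trial will ignore operation type when it assesses intraoperative difficulty, but the documents do not support that.

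A reader might also infer that the pilot comparison mostly reflects case mix. That does not hold either. Randomisation balances operation type on average, and operation type accounts for less than half of the variance in four of the six scenarios in the table. All of those times are assumed.

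Other points that stand in whole or part:

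- The pilot is descriptive and tests nothing. Its only stated planning use of clinical data is 30-day morbidity. Using pilot operative-time variability to plan the full trial would be sensible, but the protocol does not claim it.
- The 20/40/20/20 mix is a pool of potentially eligible patients, not planned enrolment. Its last fifth includes neurosurgery, although neurologic surgery is an exclusion.
- Centre stratification probably absorbs part of the cardiac imbalance. It does less for abdominal and orthopaedic cases, which are counted across all four sites.
- Objective 3 has a third measure, surgeon perceived difficulty, which is in neither minutes nor millilitres. This point does not reach it.
- The protocol also links obesity to longer operations and more blood loss in general terms, and defends operative time across kinds of surgery. By their titles, the three works cited for that defence each concern one kind of operation: distal pancreatectomy, cholecystectomy and joint arthroplasty. They fit comparison within an operation type better than a pooled mean.

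It might finally be said that covariates are a matter for the analysis plan. Here, though, the protocol itself fixes the pilot estimator, and a better one costs almost nothing.

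**Conclusion.** The point holds for the pilot's analysis only. The arm differences in operative time and blood loss will be unbiased, but less precise than they need be and open to chance imbalance in operation type. Under the assumed times, the unadjusted standard error for operative time is about 1.03 to 1.8 times the adjusted one. The lower end applies if procedures differ little or if cardiac cases all come from one centre, the upper end if they differ a lot and are spread over sites. No size was computed for blood loss, although the same reasoning applies. Nothing follows about the full-trial analysis of objective 3. This is a worthwhile improvement to a secondary, descriptive comparison and does not threaten the pilot's purpose.

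**What to change.** In the protocol section on types of analyses, state that the pilot arm differences in operative time and blood loss (and length of stay, if wished) will be estimated with 95% intervals from a linear model. Its covariates are planned-operation group (for example abdominal, orthopaedic, cardiac, other), recorded before randomisation, and centre. Report the within-group SD next to the pooled SD, so that readers can see how much of the spread comes from the operation.

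Adjustment is preferable to adding a stratification factor. Four centres by four groups would leave 88 / 16 = 5.5 patients per stratum, about the size of one block.

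The cost is one sentence, a recorded grouping and six model terms (three for group, three for centre). Residual degrees of freedom fall from 86 to 80, and the estimate becomes model-based instead of a raw difference. A log-scale analysis of operative time, reported as a ratio, is an option. It answers a slightly different question, and statisticians may reasonably differ on it.
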